### **3. Study Design**

#### **3.1 Overall Study design**

This is a phase Ib/II study including dose exploration, followed by the multi-center, open-label extended study.

The dose exploration of the Phase Ib study, a standard “3+3” design was utilized to identify the maximum tolerated dose (MTD), dose limited toxicities (DLTs) and recommended Phase II dosage (RP2D) of chidamide in combination with sintilimab. Once the MTD, DLT and RP2D of Chidamide is determined, the Phase II study shall begin.

The phase II study is proceeded according to the RP2D of chidamide. Patients that achieved CR and PR could receive for up to one-year treatment, otherwise until disease progression, death, intolerable toxicity, completion of the scheduled treatment cycle, or the investigators' decision to withdraw (whichever occurs first). After 12 months, patients still with CR or PR were allowed to choose to continue or end of treatment or accepted autologous hematopoietic stem cell transplantation (ASCT) as consolidation (Stem cell mobilization, collection, reinfusion, conditioning regimen prior to autologous hematopoietic stem cell transplantation followed the medical routine at each study site). If patients choose to continue sintilimab plus chidamide, doses of chidamide reduce to 20mg twice a week and fixed doses of 200mg sintilimab intravenously every 30 days. Dose interruptions were allowed for treatment-related adverse events until these events resolved to grade 0–1 or to baseline level. Treatment was permanently discontinued for patients who had interruptions of more than 4 weeks. Patients will be visited for end of treatment within 4 weeks after the end of the study. For those whose condition is stable or improved after treatment, progression-free survival (PFS) follow-up will be carried out 8 weeks after the last administration of the study drug, and

continued every 12 weeks thereafter until disease progression, death, withdrawal of informed consent (ICF), receiving other novel treatments, or termination of the entire study (whichever occurs first). At the same time, patients who have developed PD will be followed up for overall survival (OS) every 12 weeks until death, withdrawal of ICF, or the termination of the entire study (whichever occurs first). The survival follow-up is conducted every 8 weeks for patients with disease progression.

Patients will receive efficacy measurements, including ORR, PFS, OS, duration of response (DoR). During the entire study, efficacy will be evaluated based on International Working Group consensus response evaluation criteria in lymphoma (RECIL 2017). Patients underwent CT, MRI or whole body  $^{18}\text{F}$ -fluorodeoxyglucose (FDG) PET scans before the first treatment and then every 6 weeks up to cycle 6, and every 12 weeks thereafter. A whole-body PET scan was strongly recommended. Efficacy evaluation will be performed every 2 treatment cycles (i.e. 6 weeks) until the completion of 6 cycles of treatment, repeated every 8 weeks after 6 cycles up to 12 months, or disease progression, intolerable toxicity, death, investigators' decision, or the patient's voluntary withdrawal from the study (whichever occurs first).

Safety observation indicators include monitoring and recording of adverse events (TEAE and SAE) during treatment, performing laboratory tests (including blood routine, biochemical and urine tests), 12-lead electrocardiogram, and vital signs as specified in the design. Adverse events will be evaluated according to the NCI CTCAE (version 5.0). The safety and tolerability of the research drugs will be evaluated through laboratory and auxiliary examinations, physical and vital signs examinations. The design and flow chart of this study are shown in **Figure 1**.

[figure not shown]

Figure1. Flow chart of this study

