### 5.5 Dose adjustment

If any of the following conditions occurs, the dose of the research drug needs to be reduced in the next treatment cycle:

- Grade 4 hematotoxicity once
- Grade 3 hematotoxicity twice
- Grade 3 non-hematological toxicity once (except for alopecia).

During the combined treatment, chidamide is mainly adjusted according to hematotoxicity and non- hematotoxicity. Chidamide is reduced by 5 mg each time, and the dose could be reduced twice at most. (The standard of dose reduction is shown in the table below).

| Study Drug | Initial Dosage | First Reduction | Second Reduction |
|------------|----------------|-----------------|------------------|
| Chidamide  | RP2D (eg 30mg) | 25mg            | 20mg             |

The dose of sintilimab is not allowed to be adjusted during the entire study. The principles of suspension and permanent discontinuation of Sintilimab are shown in the Table1 below.

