**Note**

a: Resume the administration after the symptoms improvement to grade 0-1 or baseline level.

b: For hypophysitis, adrenal insufficiency, thyroid insufficiency/hypothyroidism, and type 1 diabetes, resume the administration if they are fully controlled and only need physiological hormone replacement therapy.

c: For abnormal grade 4 laboratory test results, the decision whether to terminate the medication should be determined based on the accompanied clinical symptoms or signs and the clinical judgment of the investigator.

The maximum interval allowed for drug suspension is 12-weeks. If it is not possible to recover to the state where sintilimab can be reused within 12 weeks, the subject will be permanently suspended for sintilimab administration and then enter the follow-up phase. Except for the following two cases:

- Due to the application of glucocorticoids for the treatment of irAE, sintilimab was suspended for more than 12 weeks during the process of glucocorticoid reduction. Under this condition, it is necessary to discuss with the sponsor to decide whether to continue sintilimab treatment. The radiological examination for efficacy evaluation is still carried out as planned and is not affected by the suspension of medication.
- Due to treatment of AEs unrelated to sintilimab, it was suspended for more than 12 weeks. Under this condition, it is necessary to discuss with the sponsor to decide whether to continue sintilimab treatment. The radiological examination for efficacy evaluation is still carried out as planned and is not affected by the suspension of medication.

At the beginning of each treatment course, all hematological and non-hematological toxicities must be restored to no more than Grade 1 or the baseline level and the investigator considers it appropriate to proceed to the next course. If this condition is ineligible, the administration can be extended for 14 days. Once it's over 14 days, the investigator will decide whether the patient needs to withdraw from the study based on the risk-benefit ratio.

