#### Other permissible dose adjustments of sintilimab

Under conditions other than treatment-related AEs, sintilimab treatment may be discontinued due to medical/surgical events or administrative reasons unrelated to the study. Subjects should restart the study treatment within 3 weeks after the interruption of medication, unless there are other discussions with the investigators. The reason for discontinuing medication should be recorded in the patient's study record.

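### Rules for suspension length and for chidamide dose after grade 4 haematotoxicity conflict between sections, the haemoglobin limit is reversed, and the thrombocytopenia text needs correcting

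*Protocol*

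**What the plan says.** **Length of suspension.** In section 3.1, "Dose interruptions were allowed for treatment-related adverse events" until recovery to grade 0–1 or baseline, and then "Treatment was permanently discontinued for patients who had interruptions of more than 4 weeks". No drug is named. The note below Table 1 in section 5.5 says "The maximum interval allowed for drug suspension is 12-weeks" and attaches permanent cessation of sintilimab to a later point: "If it is not possible to recover to the state where sintilimab can be reused within 12 weeks". Two exceptions may go further after discussion with the sponsor. One begins "Due to the application of glucocorticoids for the treatment of irAE, sintilimab was suspended for more than 12 weeks"; the other covers adverse events unrelated to sintilimab. The same note allows a 14-day extension at the start of a course, after which the investigator decides on withdrawal. Section 6.2 item 12 makes 14 days the maximum delay, with adverse reactions as its example.

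**Chidamide dose.** Section 5.5 lists "Grade 4 hematotoxicity once" as a trigger for reduction and then states "Chidamide is reduced by 5 mg each time, and the dose could be reduced twice at most". Its table runs from an RP2D, with 30 mg as the example, to 25 and then 20 mg. Section 5.9 sends a patient with a grade 4 haematological reaction to 20 mg per dose on resumption.

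**Thrombocytopenia.** For grade 3 or 4 events, section 5.9 says to discontinue interleukin 11 or TPO and does not expressly withhold chidamide. Section 5.9 names HUMIRA three times: in the platelet and haemoglobin resume rules and in the rule for stopping on recurrence.

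**Haemoglobin.** Criterion 8 b) in section 4.1, and the synopsis, give 90 g/L with no marrow status, then 75 g/L for patients without marrow involvement.

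**The concern.** Each of these rules decides something for an individual patient: entry, the dose on resumption, or permanent cessation. In a multicentre trial, two investigators could each follow the protocol and act differently on the same patient. Immune-related events treated with a long steroid taper are foreseen by section 5.5 itself, so long suspensions are not a remote case. The 20 mg chidamide dose is not remote either: it is the phase Ib starting level (section 5.1.1) and the dose for everyone who continues the combination after 12 months (section 5.1.2). The haemoglobin line, read literally, admits and excludes the opposite groups from those intended. At stake are patient safety and consistent conduct across sites.

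**Working it through.** No sample-size or error-rate figure is involved. The check sets the rules side by side, with simple arithmetic.

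**(a) Suspension for a treatment-related adverse event.** Inputs: 4 weeks (3.1); 12 weeks plus two exceptions (5.5, note below Table 1); 14 days = 2 weeks (6.2 item 12, and the course-start rule in 5.5); a sintilimab cycle of 3 weeks.

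| Length of suspension | 3.1 | 5.5, 12-week rule | 14-day rules |
|---|---|---|---|
| Up to 2 weeks | may resume | may resume | may resume |
| Over 2, up to 4 weeks | may resume | may resume | beyond the 6.2 maximum; 5.5 leaves it to the investigator |
| Over 4, up to 12 weeks | permanent stop | may resume | as above |
| Over 12 weeks | permanent stop | sintilimab stopped, except in two cases | as above |

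- 3.1 against the 12-week rule: 12 − 4 = 8 weeks; 8/3 = 2.67 cycles.
- 6.2 against the 12-week rule: 12 − 2 = 10 weeks; 10/3 = 3.33 cycles.
- Not every event in these ranges is in conflict. Under Other AEs, Table 1 permanently stops sintilimab for a grade 3 event that has not reached grade 0–2 or baseline within 7 days, or grade 0–1 or baseline within 14 days. For those events the rules agree on stopping.

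**(b) First grade 4 haematotoxicity.** Under 5.5, new dose = current dose − 5 mg, if fewer than two reductions have been used. Under 5.9, new dose = 20 mg. Chidamide is taken twice a week.

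| Current dose | 5.5 | 5.9 | Cut, 5.5 vs 5.9 | Weekly dose, 5.5 vs 5.9 |
|---|---|---|---|---|
| 30 mg | 30 − 5 = 25 mg | 20 mg | 5/30 = 16.7% vs 10/30 = 33.3% | 50 vs 40 mg |
| 25 mg | 25 − 5 = 20 mg | 20 mg | 20% in both | 40 vs 40 mg |
| 20 mg | 20 − 5 = 15 mg | 20 mg | 5/20 = 25% vs 0% | 30 vs 40 mg |

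At 30 mg, 5.9 makes the larger cut. At 20 mg it makes none. The 5.5 table ends at 20 mg, but it is built on an example RP2D of 30 mg, whereas the 5 mg step is stated in general terms.

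**(c) The three cytopenia rules in 5.9.**
- Neutropenia: withhold chidamide, and give G-CSF in defined cases.
- Anaemia: withhold chidamide and give EPO.
- Thrombocytopenia: discontinue IL-11 or TPO, consider transfusion, and continue treatment once platelets recover to 75 × 10⁹/L.

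The third breaks the pattern of the other two: the verb has attached to the supportive drug. HUMIRA is not a study drug, and the context shows that chidamide is meant.

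**(d) Lower limits in criterion 8.**

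| Item | Higher limit | Lower limit | Group given the lower limit |
|---|---|---|---|
| Neutrophils | 1.5 × 10⁹/L | 1.0 × 10⁹/L | with marrow involvement |
| Haemoglobin | 90 g/L | 75 g/L | **without** marrow involvement |
| Platelets | 75 × 10⁹/L | 50 × 10⁹/L | with marrow involvement |

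The Amendment 01 rationale says that the change was made to describe haematological function in patients with marrow involvement. Read literally, someone with haemoglobin of at least 75 and below 90 g/L (a band of 15 g/L) is eligible if the marrow is not involved and ineligible if it is.

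**The case against.** **Section 5.5 is the detailed sintilimab section and 3.1 is an overview, so sites would follow 5.5.** This is a reasonable reading, but no precedence is stated. Section 3.1 names no drug, and it uses essentially the same recovery standard as 5.5. Confining the 4-week limit to chidamide would remove the conflict, but the text does not say so. That sites would in fact diverge is a possibility, not something the protocol shows.

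**The 3-week restart rule might look like a further conflict.** It is not. "Subjects should restart the study treatment within 3 weeks after the interruption of medication" stands under other permissible dose adjustments in section 5.6 and covers interruptions for reasons other than treatment-related events.

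**The two-reduction limit in 5.5 might seem to contradict the stop rule in 5.9.** The documents do not support that. At most two reductions is a ceiling, not an entitlement, and it is compatible with stopping earlier on recurrence. A clarifying sentence is useful, but there is no error here.

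**A reader might infer that 5.9 keeps chidamide going through severe thrombocytopenia.** That goes too far. The paragraph says when treatment can continue and gives the dose on resumption, both of which presuppose a hold. The neighbouring rules state the hold outright, and sections 5.5 and 6.2 require acceptable results before dosing. What stands is a wrong verb and a wrong drug name, with one sensible reading.

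**The four items are unrelated and differ in weight.** This is fair. The case for an amendment rests on (a), (b) and (d); (c) is an editorial correction to make at the same time.

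**Conclusion.** The point holds for the current text.

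- **(a)** The stopping rules disagree for sintilimab suspensions of more than 4 and up to 12 weeks, and in the two exceptions beyond 12 weeks. The 14-day maximum in 6.2 starts the disagreement earlier. Events that Table 1 already stops are outside it, so it would be wrong to say that every suspension of 4 to 12 weeks is affected.
- **(b)** The chidamide dose conflicts at 30 mg (25 vs 20 mg) and at 20 mg (15 vs 20 mg), with no conflict at 25 mg. The 20 mg result assumes that two reductions have not already been used and that the 5 mg step is not limited by the example table.
- **(c)** Wording corrections only.
- **(d)** The haemoglobin limit is attached to the wrong marrow group.

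The protocol gives no frequency for any of these situations, so no number of affected patients can be stated. Nor do they change the stated alpha, power or sample size. The point should be fixed because literal application would misdirect eligibility, dosing or stopping, and correction is cheap.

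**What to change.** - **(a)** In 3.1 and 6.2, refer sintilimab suspension to the 12-week rule in 5.5, its two exceptions and the Table 1 stops. State which drug the 4-week limit applies to. State that 14 days is a cycle-delay limit leading to investigator review. Leave the 3-week restart rule in 5.6 as it is.
- **(b)** Keep one chidamide reduction rule for grade 4 haematotoxicity and state the action at 20 mg. Add that the 5.9 stop rule applies whether or not two reductions have been used, in both of its limbs: recurrent grade 4 haematological reaction, or recurrent grade 3 neutropenia with temperature above 38.5°C.
- **(c)** For grade 3 or 4 thrombocytopenia, write that chidamide is withheld and IL-11 or TPO is given. Keep the transfusion clause, and replace HUMIRA with chidamide in all three places in 5.9.
- **(d)** In criterion 8 b) and the synopsis, require haemoglobin of at least 90 g/L without marrow involvement and at least 75 g/L with it, keeping the 14-day transfusion condition.

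The cost is one wording amendment with the usual ethics committee approval (section 11.5). It needs no new visits, procedures or patients. The sponsor and investigators must make two clinical choices: which chidamide reduction rule to keep, and what the 4-week limit covers.

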## **6.2 Visits during the treatment period**

1. Vital signs.
2. Physical examination.
3. Weight measurement.
4. Laboratory examination: Before each medication administration during the treatment period, the laboratory examination must be completed and the blood sampling time should not be earlier than 48 hours before the medication. Only when the investigator determined the laboratory examination results qualified can the subjects continue medication. During the treatment period, the investigator can increase the frequency of blood routine examinations

according to the conditions of the subjects.

5. Plasma EBV-DNA monitoring: Monitored on the first cycle of treatment and the first day of subsequent cycle. After all treatment courses are completed, monitored once a month at a fixed time.
6. 12-lead electrocardiogram: Evaluated every 3 weeks ( $\pm 3$  days) from the first administration.
7. Cardiac ultrasound examination (including evaluation of left ventricular ejection function): evaluation will be carried out every 12 weeks ( $\pm 7$  days) from the first administration.
8. Thyroid function: Evaluated every 3 weeks ( $\pm 3$  days) from the first administration.
9. Pulmonary function: Evaluated every 12 weeks ( $\pm 7$  days) from the first administration or there may be clinical needs.
10. Bone marrow examination (smear  $\pm$  biopsy): Evaluated every 6 weeks ( $\pm 7$  days) from the first administration for those with bone marrow infiltration or there may be clinical needs.
11. Tumor evaluation: Baseline and follow-up evaluations should adopt the same radiological methods and be performed by the same investigator as far as possible. Tumor assessment will be calculated according to the actual date of medication before each medication and will be evaluated every 6 weeks ( $-7$  days), regardless of the effect of drug withdrawal. For patients who are suspected of developing PD before the next scheduled evaluation, an extra tumor evaluation should be performed.
12. Administration of the research drug: Administered every 3 weeks. If the subject cannot take the medicine at the planned time due to special reasons

(such as adverse reactions), a maximum delay of 14 days is allowed.

13. Record the combined medication;

14. Record AE.

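### For a treatment-related adverse event the protocol sets conflicting limits on interruption: permanent stop after 4 weeks (3.1), sintilimab suspension up to 12 weeks (5.5), delay of at most 14 days (6.2)

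*Protocol*

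**What the plan says.** Three places in the current protocol text limit how long treatment may be interrupted for an adverse event.

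- **Section 3.1.** "Dose interruptions were allowed for treatment-related adverse events until these events resolved to grade 0–1 or to baseline level". The next sentence reads: "Treatment was permanently discontinued for patients who had interruptions of more than 4 weeks". It names no drug and gives no exception.
- **Section 5.5, text below Table 1.** "The maximum interval allowed for drug suspension is 12-weeks". The consequence, worded for sintilimab, follows: "If it is not possible to recover to the state where sintilimab can be reused within 12 weeks, the subject will be permanently suspended". There are two exceptions: a glucocorticoid taper for an immune-related event, and AEs unrelated to sintilimab. In both, a longer suspension is possible: "Under this condition, it is necessary to discuss with the sponsor to decide whether to continue sintilimab treatment".
- **Section 6.2, item 12.** If a dose cannot be given as planned, with adverse reactions as the example, "a maximum delay of 14 days is allowed". No discretion is provided.

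The end of section 5.5 adds a course-start condition. Toxicity must be back to Grade 1 or baseline, and a 14-day extension is allowed. Then: "Once it's over 14 days, the investigator will decide whether the patient needs to withdraw from the study". Section 5.6 has a separate rule for holds not caused by treatment-related AEs: "Subjects should restart the study treatment within 3 weeks after the interruption of medication", unless otherwise discussed with the investigators.

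**The concern.** The sections cover the same event and use the same recovery criterion, but they give different limits. Section 3.1 deals with treatment-related events that must return to Grade 0–1 or baseline. Table 1 deals with sintilimab-related events, and its footnote a resumes dosing on the same criterion.

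Three things depend on the limit:

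- Whether a patient is re-treated after an immune-related event.
- Section 5.12 item 1, which makes stopping mandatory when a treatment-related AE meets the protocol's discontinuation criteria. Where those criteria conflict, a site cannot tell whether stopping is mandatory, and a monitor cannot tell whether continuing is a deviation.
- Section 8.1, which lists permanent discontinuation for a treatment-emergent event among the safety endpoints. In a multicenter trial the count could differ between sites simply because they follow different sections.

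**Working it through.** The protocol gives no figure to reproduce. The check puts the limits on one scale and follows one patient through each rule.

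**Scale.** Section 3.1: 4 × 7 = 28 days. Section 5.5: 12 × 7 = 84 days. Section 6.2: 14 days. The first two differ by 84 − 28 = 56 days, a factor of 84 / 28 = 3.

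**Test patient.** A first Grade 2 pneumonia related to sintilimab, suspended under Table 1 footnote a, returns to Grade 0–1 after 8 weeks (56 days). The event has its own row in Table 1, so the 7/14-day recovery rule for other Grade 3 AEs does not apply.

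| Place | Limit | Result at 56 days |
|---|---|---|
| 3.1 | more than 28 days | permanent discontinuation |
| 5.5, 12-week rule | 84 days | may resume |
| 6.2 item 12 | 14 days | maximum already exceeded |
| 5.5, course start | 14 days, then discretion | investigator decides |
| 5.6, non-AE rule | 3 weeks, can be waived | does not apply |

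**Does the starting point remove the conflict?** Section 6.2 counts from the planned dose. Sections 3.1 and 5.5 do not say where their intervals begin. Sintilimab is given every 21 days, so each could begin at the last dose or at the first missed dose, 21 days later. The window in which 3.1 stops and 5.5 permits resumption, in days since the last dose, is:

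- both counted from the last dose: over 28 and up to 84, a width of 56;
- both counted from the missed dose: over 28 + 21 = 49 and up to 84 + 21 = 105, a width of 56;
- 3.1 from the missed dose and 5.5 from the last dose: over 49 and up to 84, a width of 35;
- 3.1 from the last dose and 5.5 from the missed dose: over 28 and up to 105, a width of 77.

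The window never closes. The test patient falls inside it in all four cases. If the 56 days run from the last dose, 56 lies between 49 and 84. If they run from the missed dose, that is 56 + 21 = 77 days since the last dose, also between 49 and 84.

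**Does the drug remove the conflict?** The 12-week rule is worded for sintilimab, whereas 3.1 speaks of treatment, which includes sintilimab. No sentence restricts 3.1 to chidamide or to holding both drugs together.

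**The case against.** Much of the apparent disorder disappears on a careful reading. Several stronger readings that a reader might infer are not supported.

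- **Four competing limits for the same patient.** The 3-week rule in 5.6 covers reasons other than treatment-related AEs, can be waived by discussion, and imposes no permanent stop. It does not compete for a treatment-related event.
- **A 4-week rule that applies whatever the reason.** The preceding sentence in 3.1 most naturally ties it to treatment-related AEs. That reading narrows the rule but places it exactly where Table 1 and the 12-week rule operate.
- **Table 1's 7/14-day rule and the course-start clause as contradictions.** The first is a stricter event-specific criterion under a general ceiling. The second triggers an investigator decision and is not itself a maximum. Both can work inside either ceiling.
- **Every hold between 4 and 12 weeks treated differently by 3.1 and 5.5.** This is not so. Some of these patients have already been stopped by Table 1, which is part of 5.5.
- **A six-fold spread (84 / 14).** This may not compare like with like. If the 12 weeks run from the last dose, a 14-day delay is 21 + 14 = 35 days, or 5 weeks, and the ratio is 12 / 5 = 2.4.
- **An effect on the response rate.** None is shown. Tumor evaluation continues during suspension (5.5, 6.2, 7.2), and patients who stop early for intolerance keep radiological follow-up (6.4). The median time to response with chidamide alone in section 1.1 is 5.9 weeks (1.1 to 8.1), which suggests limited room for one.

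All of these objections stand. None reconciles 3.1 with the 12-week rule in 5.5, or either of them with the 14-day maximum in 6.2.

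**Conclusion.** The protocol contradicts itself on the longest interruption allowed for a treatment-related adverse event. The decisive conflict is 4 weeks in 3.1 against 12 weeks, with extensions, in 5.5. The 14-day maximum in 6.2 is a second conflict.

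The limits in 3.1 and 5.5 are 56 days apart on a common starting point. The window of opposite instructions is 35 to 77 days wide over the possible starting points, assuming the 21-day cycle.

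The number of patients affected cannot be derived, because the protocol gives no rate of long holds. A count such as 5% to 20% of the 28 phase II patients (1.4 to 5.6) would only restate an assumed rate. The finding therefore concerns re-treatment after related events, the mandatory-stop criterion and the discontinuation count in 8.1. It does not show a bias in the response rate, and it takes no position on which limit is clinically right.

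**What to change.** Reconcile sections 3.1, 5.5 and 6.2 item 12 into one stated rule that gives:

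- the drug or drugs it covers;
- the reason for interruption;
- the point from which the interval is counted;
- its precedence relative to the event-specific rules in Table 1, the course-start clause at the end of 5.5, and the separate non-AE rule in 5.6.

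The other sections should refer to this rule and not restate a limit. The sponsor's medical lead chooses the limit.

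The 8.1 endpoint needs no new scoring rule. Permanent discontinuations should still be counted as they occur, with the primary reason recorded as 5.12 requires. Deriving the count from a rule could misstate what happened.

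The cost is wording in a few sections, with no change to sample size or analysis.
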